# Patients with lumbar spinal stenosis who will undergo uniportal endoscopic decompressive laminectomy

- Target sample size: 120 subjects (Study group: 60 subjects, Control group: 60 subjects, including 20 % drop-out rate)
- Primary outcome: ODI (Oswestry disability index)
- According to a previous study [1], the MCID (Minimal clinical important difference) of ODI was 12.8 and in another previous study [3], the standard deviation of the ODI value at 1 year after decompressive laminectomy was 18.8. Assuming an equivalence limit of 12.8, under the conditions of alpha = 0.05, power = 0.90, two-sided 95% confidence interval, and follow-up loss at 20%, 60 participants are needed in each group.

[figure not shown]

Subject Recruitment Plan

This is a prospective, multicenter study which will recruit subjects at the Department of Neurosurgery of Seoul St. Mary’s Hospital, Chundam Woorideul Spine Hospital and the Wiltse Memorial Hospital (Anyang). Those who are planning to undergo one-segment or two-segment decompression surgery for lumbar spinal stenosis will be recruited as subjects and advertisement for subject recruitment will not be used.

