General principles of analysis

- For continuous variables, descriptive statistics (number of subjects, mean, standard deviation, median, minimum, maximum) are presented, and for categorical variables, frequency (N) and percentage (%) are presented.

- In the analysis of the primary efficacy endpoint, if missing data occurs due to dropout, etc., the data are processed as a failure and the non-responder imputation (NRI) method is used.

- If the clinical trial is discontinued according to the discontinuation criteria, the data are handled as missing values.

- In the analysis of secondary efficacy endpoints, when there are missing values in the data, a method of last observation carried forward (LOCF) is used.

- For the analysis of the safety set, when there are missing values in the data, the data shall be analyzed as it is without performing imputation for the missing values (OC method).

Handling of analysis sets

- The analysis sets are categorized into safety set, full analysis set (FAS) and per protocol (PP) set.

- Efficacy data are analyzed using both FAS and PP, and final determination on efficacy endpoints is conducted by FAS analysis based on the modified ITT (intention to treat).

- Data on safety are analyzed for the safety sets.

- For the analysis of efficacy endpoints, when there are missing values in the data, the data shall be analyzed as it is without performing imputation for the missing values.

Definition of analysis sets

• FAS (Full Analysis Set): Subjects who met the inclusion/exclusion criteria and who underwent randomization to receive the intervention at least once during the trial period are included in FAS. In the efficacy analysis, regardless of the actual status of undergoing the surgery, analysis is performed based on the treatment group assigned by randomization.

• PP (Per Protocol Set): Subjects who have completed the trial without major protocol violations among the full analysis set (FAS) are included in PP set. However, if the trial is discontinued according to the discontinuation criteria, the clinical trial is considered to be completed and included in the PP analysis. For items of major protocol violations, see Section 13-5.

• Safety Set: Subjects who were randomized and have undergone the surgery at least once during the trial period are included in the safety set. In the safety analysis, analysis is performed based on the classification according to the actual type of surgery received.

|  | | | | | | |

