2. The investigator will take necessary medical action.

If the subject requires emergency measures due to this study, the necessary emergency measures shall be taken as soon as possible. In addition, in the case of serious adverse events (SAEs), prompt and appropriate actions shall be taken to minimize possible damage. However, general complications expected after lumbar spinal surgery are not considered as complications “caused by this study.”

* Discontinuation•Drop-out Criteria

The principal investigator may consider discontinuation of the clinical study in the following cases.

1. In the event of serious adverse events (SAEs) in subjects
2. Other cases where the investigator deems that continuation of the study may be difficult

The cases for consideration of subject dropout are as follows.

1. Non-compliance to the instructions of the investigator
2. If the subject or LAR withdraws the consent to participate (presented explicit wishes to refuse the participation in the study)
3. Violation of the inclusion/exclusion criteria
4. In the event of serious adverse events SAEs/adverse device effect (ADE)
5. Other cases where the investigator deems that continuation of the study may be difficult

In the event of a withdrawal or dropout of a subject, the investigator must make every effort to follow-up the study subject who has withdrawn or dropped out for any reason, and must perform a follow-up monitoring evaluation for safety.

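### Equivalence is decided on the FAS alone, and the per-protocol set that should check it counts discontinued subjects as completers while their data are set to missing

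*Protocol*

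**What the plan says.** The Protocol's primary objective is equivalence of endoscopic and conventional surgery. Under Primary Endpoint, equivalence is declared if the 95% CI for the between-group difference in 12-month ODI lies within ±12.8. That rule does not mention the PP set.

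- **Deciding set** (Handling of analysis sets). Both FAS and PP are analysed, but "final determination on efficacy endpoints is conducted by FAS analysis based on the modified ITT".
- **FAS** (Definition of analysis sets). "Subjects who met the inclusion/exclusion criteria and who underwent randomization to receive the intervention at least once during the trial period are included in FAS". Patients are then analysed in their allocated group, whether or not that surgery took place.
- **PP** (Definition of analysis sets). PP consists of FAS members who completed without major violations. An exception follows: "if the trial is discontinued according to the discontinuation criteria, the clinical trial is considered to be completed and included in the PP analysis".
- **Data after discontinuation** (General principles of analysis). "If the clinical trial is discontinued according to the discontinuation criteria, the data are handled as missing values".
- **Missing primary data.** General principles of analysis counts them as failures (non-responder imputation, NRI). Handling of analysis sets says missing efficacy data are not imputed.
- **Discontinuation and drop-out criteria.** There are two lists. The discontinuation list has two entries: serious adverse events and investigator judgement. The subject drop-out list repeats both and adds non-compliance, withdrawn consent and "Violation of the inclusion/exclusion criteria". The section then asks for every effort to follow subjects who withdraw or drop out.

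**The concern.** In a superiority trial, as-randomised analysis is usually the cautious choice, because patients who do not receive their allocated treatment dilute the effect. In an equivalence trial the same dilution moves the estimate towards the conclusion the trial hopes to reach. An endoscopic case converted to open surgery, or a patient operated on by the other technique, stays in the allocated arm and makes the arms look more alike. The usual safeguard is to require a PP analysis to agree. Here PP is reported but cannot block a claim.

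The PP set is also weakened by its own definition. The exception lets a subject discontinued for a serious adverse event or by investigator judgement count as a completer, while the data rule sets that subject's values to missing. PP can therefore include subjects with no usable 12-month ODI, and an ODI actually collected after discontinuation is discarded. At stake is whether an equivalence claim could survive imperfect delivery of the allocated surgery without the planned analyses showing it.

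**Working it through.** **Inputs** (Protocol, Statistical Consideration)
- Margin 12.8, alpha 0.05, power 0.90: "Assuming an equivalence limit of 12.8, under the conditions of alpha = 0.05, power = 0.90, two-sided 95% confidence interval".
- SD 18.8: "the standard deviation of the ODI value at 1 year after decompressive laminectomy was 18.8".
- Loss and group size: "follow-up loss at 20%, 60 participants are needed in each group". Evaluable per arm: 60 × 0.8 = 48.

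**Reproducing the planned size.** An exact t-based two one-sided tests calculation at 0.05 per side (equivalent to a 90% CI), with true difference 0, gives 48 evaluable per arm, and 48/0.8 = 60. The stated 60 is reproduced. At 0.025 per side, which is what the 95% CI rule implies, the same calculation gives 58 evaluable, and 58/0.8 = 72.5, so 73 per arm. With 48 per arm, power is 90.4% with a 90% CI and 82.0% with a 95% CI.

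**Effect of dilution on the FAS decision**
1. SE = 18.8 × √(2/48) = 3.84.
2. The 95% CI lies within ±12.8 only if |estimate| < 12.8 − 1.986 × 3.84 = 5.18 (from unrounded values).
3. Take the true difference between operations, as delivered, to equal the margin. If a share x of the contrast is lost, the FAS difference is 12.8 × (1 − x).
4. P(false equivalence) = P(|N(12.8(1 − x), 3.84)| < 5.18).

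| Assumed dilution x | FAS difference | P(false equivalence) |
|---|---|---|
| 0 | 12.80 | 2.4% |
| 5% | 12.16 | 3.4% |
| 10% | 11.52 | 4.9% |
| 20% | 10.24 | 9.4% |

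Allowing for estimation of the SD gives 2.5%, 3.6%, 5.2% and 9.7%. With 60 per arm the last three become 3.8%, 5.6% and 11.1%. Crossover of 5% in each arm corresponds to x = 10%, and of 10% in each arm to x = 20%.

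The dilution rates are assumed; the Protocol gives no conversion or crossover rate. The model also assumes that a patient who has the other operation gets that operation's average outcome.

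**The discontinuation rules side by side.** The PP exception makes a discontinued subject a completer. The data rule makes the same subject's values missing. The NRI rule would then count the subject as a failure, and the no-imputation rule would leave the subject out of the estimate. The text does not say which applies, so the direction of any resulting bias cannot be fixed.

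**The case against.** The strongest reply is that the scope for dilution is small. Treatment is a single operation, and the surgeon learns the allocation immediately beforehand. At 5% dilution the error rises by about one percentage point, and only if the true difference sits at the margin. This stands as a limit on size; it does not give PP a role in the decision.

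A reader might infer more than the text supports:
- **That non-compliant or ineligible subjects stay in PP.** The exception cites the discontinuation criteria, while those two grounds appear only in the drop-out list. FAS membership requires eligibility and PP is drawn from the FAS. The exception relaxes completion and does not say it waives the bar on major violations. The list of violations is in a section not at hand, so it cannot be said that crossovers remain in PP.
- **That the worst outcomes are removed from the comparison.** That follows only under the no-imputation rule; under NRI the same subjects count as failures.
- **That the FAS definition contradicts itself.** It can be read as randomised to receive the intervention, which fits as-randomised analysis. The Safety Set wording, which plainly requires surgery, supports that reading. The FAS wording is unclear at most.

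The exception literally speaks of the trial being discontinued, so a trial-level reading is possible. In a definition of which subjects enter PP, the subject-level reading is the natural one, but the ambiguity itself needs correcting.

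Finally, limiting PP to observed 12-month ODI loses some discontinued subjects selectively. That is fair, and it is why PP should join the FAS in the decision and not replace it.

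**Conclusion.** The point holds in two parts. First, the FAS alone decides equivalence although dilution there favours the claim, and PP has no say. This is explicit in the text. Second, on the subject-level reading, the PP exception and the missing-data rule together admit completers without a 12-month ODI and discard values observed after discontinuation. How those subjects enter the primary analysis is unresolved, because NRI and no imputation are both stated.

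The size is conditional. With a true difference at the margin, 10% dilution roughly doubles the false-equivalence probability (2.4% to 4.9%) and 20% roughly quadruples it (to 9.4%). These figures rest on assumed dilution rates, SD 18.8 and 48 evaluable per arm. The sponsor should correct this before analysis; the documents do not show that the actual bias would be large.

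**What to change.** 1. Declare equivalence only if the 95% CI lies within ±12.8 in both the FAS and the PP set.
2. Delete the sentence that counts discontinued subjects as PP completers. Limit PP to subjects who had the assigned operation, no major violation and an observed 12-month ODI.
3. In the FAS, use any 12-month ODI obtained after discontinuation instead of setting it to missing. The existing follow-up duty makes this feasible.
4. State that the FAS is all randomised patients, analysed as randomised.

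The conflict between NRI and no imputation also has to be settled, so that subjects with no 12-month ODI are handled in one stated way.

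**Cost.** These are wording changes, plus some loss of power from requiring both sets. With 48 evaluable per arm in PP, power under the 95% CI rule is at most about 82%. Most of the gap from 90% already exists with the FAS alone, because the planned 60 per arm matches a 90% CI. Restoring 90% power in PP would need 58 evaluable per arm, or 73 randomised per arm at 20% loss.

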Before surgery, conduct pre-surgery radiological assessment, clinical physical examination (age, gender) and medical history taking (disease history, surgical history) for these subjects, and check the results of the clinical laboratory tests (CBC, Routine chemistry). Check for complications based on radiological imaging tests (X-ray) before surgery, immediately after surgery (X-ray, MRI or CT), and 2 weeks, 3 months, 6 months and 12 months after the surgery. Perform clinical assessments by conducting questionnaires on VAS, ODI, EQ5D, gait, satisfaction, and POSAS before surgery and 2 weeks, 3 months, 6 months and 12 months after the surgery. Immdiately after the surgery, take measurements on the items related to the surgery (postsurgery bleeding, duration of surgery, hospital stay, Creatine Kinase (CK, CPK) at postoperative day 1) to compare surgery-related items.

- However, if the subject is unable to visit the site at planned dates due to unavoidable reasons (such as safety issues due to COVID-19), non-face-to-face treatment or telephone surveys permitted by the current laws can replace the actual outpatient visit.

Eligibility:

Patients with ≥ grade B lumbar central canal stenosis who agree to undergo one to two segment posterior spinal decompression surgery, those who can be followed up for at least 1 year.

Inclusion Criteria:

1. Ages 20 to 80
2. Patients ≥ grade B lumbar central canal stenosis who agree to undergo one to two segment posterior spinal decompression surgery
3. Those who can be followed up for at least 1 year
4. Subjects who signed the informed consent form on own (if the subject is able) or through a legally authorized representative after fully understanding the details of the clinical trial

Exclusion Criteria:

1. Patients with spondylolisthesis (Meyer grade ≥ II)
2. Those who have had the same segmental surgery
3. Degenerative lumbar scoliosis (Cobb angle > 20°)
4. Cause of the lumbar spinal stenosis is not of degenerative nature or it is caused by lumbar disc herniation
5. Presence of other spinal disorders in the lesions of the lumbar spinal stenosis (e.g. ankylosing spondylitis, spinal tumor, spinal fracture)
6. Psychological disorders (such as dementia, intellectual disability, or drug abuse)
7. Those who have refused to participate in the study
8. Other patients deemed ineligible by the investigator to participate in the clinical trial

Treatment Plan:

- Surgical Method

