This study will be conducted by dividing the patients with lumbar spinal stenosis who will undergo posterior spinal decompression surgery into the interlaminar full-endoscopic laminectomy group (group 1) and conventional surgery group (group 2) through a prospective, randomized trial. Interlaminar full-endoscopic laminectomy is currently the preferred minimally invasive surgery method. Unilateral laminectomy bilateral decompression (ULBD) is a minimally invasive surgical method without endoscopy, and the clinical outcomes have been reported to show no significant difference from those of conventional surgical techniques. Therefore, it is necessary to verify the equivalence in clinical outcomes between the interlaminar full-endoscopic laminectomy and the conventional open decompressive laminectomy.

This is a prospective study, and among the subjects who voluntarily gave their consent to participate in the study and signed the ICF, those who are eligible according to the inclusion and exclusion criteria will be randomized to one of the two groups at a ratio of 1:1. The permuted block randomization method is used for randomization. Randomization is applied in sequence from subject number 1 using iCReaT, a web-based eCRF. The investigator will perform the surgery according to the results of randomization of the subjects. To minimize possible bias that may arise, randomization is performed by a researcher from the Department of Neurosurgery, and the surgeon is informed of the randomization code immediately before surgery.

This study has limitations in applying the double-blind method. It is inevitable that the investigator knows which procedure was used, and the patient also knows the surgical method due to the incision site after surgery. Therefore, the assessor-blind method, which applies the blinding only to the assessor, is applied, and an assessor is a third person who has not performed the surgery.

Statistical Consideration:

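### The FAS that decides equivalence is conditional on having met the entry criteria, with no rule that a violation be objective, pre-date randomisation or be judged blind to arm and outcome

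*Protocol*

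**What the plan says.** The Protocol, under *Definition of analysis sets*, limits the FAS to "Subjects who met the inclusion/exclusion criteria and who underwent randomization to receive the intervention at least once during the trial period". The next sentence says that, in the efficacy analysis, "regardless of the actual status of undergoing the surgery, analysis is performed based on the treatment group assigned by randomization". Under *Handling of analysis sets*, efficacy is analysed in both FAS and PP, and the FAS analysis, described as modified ITT, is decisive. The PP set consists of FAS members who completed without major violations. The safety set is not used for efficacy.

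Four other places bear on how the eligibility condition would work:

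- *Exclusion Criteria*, item 8: "Other patients deemed ineligible by the investigator to participate in the clinical trial". Items 4 and 5 concern the cause of the stenosis, including disc herniation, and other spinal disorders at the lesion.
- *Discontinuation/Drop-out Criteria*: the cases in which dropout of a subject is considered include "Violation of the inclusion/exclusion criteria".
- *Setting the control group and randomization method*: "It is inevitable that the investigator knows which procedure was used". Only the assessor is blinded.
- *Schedule of Activities*: eligibility is checked at Visits 1 and 2. Randomisation and surgery take place at Visit 2, and the two visits may coincide.

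**The concern.** If only eligible patients are randomised, as *Study design* intends, the eligibility condition removes nobody. It takes effect only when a violation is recognised later, and the drop-out list shows that the Protocol foresees violations among enrolled subjects. The definition then removes the patient from the decisive set. It does not ask whether the fact existed before randomisation, whether it is objective, or whether the person judging it knew the arm or the result.

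Most criteria, such as age, slip grade, Cobb angle and earlier surgery at the same segment, are baseline facts that leave little room for judgement. Exclusion 8 has no objective content. Exclusions 4 and 5 could be re-read in the light of operative findings. An investigator who knows the procedure could apply any of these three after allocation.

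The PP set cannot show the effect of such removals, because it is a subset of the FAS. The direction also matters in an equivalence trial: losing poor outcomes from the worse arm pulls the difference towards zero and favours the claim.

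**Working it through.** **Inputs from the Protocol.** *Statistical Consideration*: SD of 1-year ODI 18.8, margin 12.8, 60 per group, 20% follow-up loss, alpha 0.05, power 0.90. *Primary Endpoint*: equivalence is declared if the two-sided 95% CI lies within ±12.8.

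**Assumed inputs.** The Protocol gives no count of eligibility removals. I take k = 1 to 5 patients, all from the worse arm, all with a 12-month ODI, and D = 20 to 30 points worse than the rest of that arm (20/18.8 = 1.1 to 30/18.8 = 1.6 SD).

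**The plan's own figure.** For equivalence with a true difference of 0, n = 2[SD(z(1−α) + z(1−β/2))/margin]². With α = 0.05 per side this is 2[18.8 × (1.645 + 1.645)/12.8]² = 46.7, so 47, and 47/0.8 gives 59. The t-based version gives 48, and 48/0.8 = 60, which is the stated size. With α = 0.025 per side, which matches the stated 95% CI, the t-based size is 58, or 73 after inflation. That mismatch is a separate matter. Here the calculation only supplies the arm size of 60 × 0.8 = 48.

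**Room inside the margin, 48 per arm.**
- SE = 18.8 × √(2/48) = 3.84
- 95% half-width = 1.9855 × 3.84 = 7.62
- Room = 12.8 − 7.62 = 5.18 points
- At a true difference of 12.8, P(equivalence) ≈ Φ((5.18 − 12.8)/3.84) = 2.4%

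**Effect of removal.** The arm mean shifts by kD/48, and P ≈ Φ((5.18 − 12.8 + shift)/3.84). The simulation used 100,000 runs and the reduced arm size.

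| k | D | Shift | Approximate P | Simulated P |
|---|---|---|---|---|
| 0 | – | 0 | 2.4% | 2.5% |
| 1 | 20 | 0.42 | 3.0% | not run |
| 2 | 20 | 0.83 | 3.9% | 3.9% |
| 3 | 20 | 1.25 | 4.9% | 5.0% |
| 5 | 20 | 2.08 | 7.5% | 7.6% |
| 5 | 30 | 3.12 | 12% | 11.8% |

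With 60 per arm, the simulated values for 0 removed and for the last four rows are 2.6%, 3.9%, 4.6%, 6.8% and 10.6%. The shift takes up between 0.42/5.18 = 8% and 3.12/5.18 = 60% of the room.

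**Which patients this covers.** The 48 per arm is already net of follow-up loss, so the figures apply only to patients who were operated on, followed to 12 months and later called ineligible. In practice that means exclusions 4, 5 and 8.

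**The case against.** The strongest reply is that eligibility is settled before randomisation. *Study design* randomises only eligible, consenting patients, and the schedule has no eligibility check at follow-up. On that reading exclusion 8 belongs to screening and the clause is nearly empty. This stands as a description of intent, and it suggests that removals would be few. The definition itself does not say so, however, and the drop-out list expects violations.

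A reader might also infer that inclusion 3 ("those who can be followed up for at least 1 year") lets any patient lost to follow-up be reclassified as ineligible. The documents do not support this. The criterion is a judgement at entry, the sample size allows for 20% loss, there is a rule for primary data missing through dropout, and the PP set is the completers within the FAS. Lost patients are therefore meant to be FAS members. Likewise, a later refusal does not fall under exclusion 7, because withdrawal of consent is a separate item in the drop-out list.

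Nor does the drop-out list say that violations are found after the operation. It gives no timing, lists cases for consideration only, and asks for every effort to follow those who leave. Discovery at operation under exclusions 4 and 5 is an inference.

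Finally, who adjudicates eligibility may properly be left to the SAP, and its absence here is no fault. The membership rule itself, though, is fixed in the Protocol, without a safeguard.

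**Conclusion.** The point holds as a defect in how the decisive set is defined. It should be corrected, but it is not evidence that bias will occur. Bias arises only if removals are related to arm or outcome. The range of about 3% to 12%, against 2.4%, is an illustration: it rests on assumed numbers of removals, on an assumed ODI deficit, and on all removals coming from the worse arm. With a single patient 20 points worse the rise is only to about 3%. It should not be read as an effect of loss to follow-up or withdrawal of consent, which the Protocol handles as dropout within the FAS.

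**What to change.** Under *Definition of analysis sets*, define the FAS as all randomised patients analysed as allocated, whether or not they had surgery and whether or not an eligibility violation is found later. Handle violators in the PP set or a sensitivity analysis. The FAS should not be limited to patients who were operated on. The surgeon learns the allocation immediately before surgery, so that limit would be an exclusion made with the arm known, and it would conflict with the Protocol's own rule of analysis by allocation.

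If any eligibility exclusion from the FAS is kept, limit it to objective criteria with source data dated before randomisation, have it decided blind to arm and outcome, and rule out exclusion 8 as a ground.

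Under *Discontinuation/Drop-out Criteria*, state that an eligibility violation does not end ODI follow-up. This agrees with that section's own requirement to keep following those who leave.

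The cost is wording in two places. A few ineligible patients would add slight noise to the primary set, and the PP analysis would still show the result without them.

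### A serious adverse event can be labelled discontinuation or dropout; the two labels have conflicting data rules, and neither secures the 52-week ODI

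*Protocol*

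**What the plan says.** The Discontinuation and Drop-out Criteria contain two lists. The first opens "The principal investigator may consider discontinuation of the clinical study in the following cases", and its first item is "In the event of serious adverse events (SAEs) in subjects". The second opens "The cases for consideration of subject dropout are as follows", and its fourth item is "In the event of serious adverse events SAEs/adverse device effect (ADE". The same catch-all, that the investigator judges continuation to be difficult, closes both lists. The section ends with a duty on the investigator after withdrawal or dropout. Its first part is "must make every effort to follow-up the study subject who has withdrawn or dropped out for any reason". Its second part, the only one to name an evaluation, is "must perform a follow-up monitoring evaluation for safety".

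The consequences for the data are set elsewhere in the protocol:

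- General principles of analysis: a primary value missing through dropout is counted as a failure by non-responder imputation (NRI). The next rule is "If the clinical trial is discontinued according to the discontinuation criteria, the data are handled as missing values".
- Handling of analysis sets: missing efficacy values are not imputed, and the FAS, on a modified ITT basis, decides efficacy.
- Definition of analysis sets: PP membership requires completion without major violations, but "if the trial is discontinued according to the discontinuation criteria, the clinical trial is considered to be completed and included in the PP analysis".
- Primary Endpoint: the endpoint is the ODI change from baseline to 12 months, and equivalence requires the 95% CI for the treatment difference to lie within ±12.8.

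**The concern.** The intervention is one operation on day 0. After it there is no continuing study treatment, so calling a patient a dropout because of a later SAE in practice means ending assessments. Patients with serious complications, including those who need revision surgery, are plausibly among the poor outcomes that the trial sets out to compare.

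The protocol gives no rule for choosing between the two labels, and the choice changes both the primary data and the PP status. It rests with an investigator who, as the section on the control group and randomization accepts, cannot avoid knowing which procedure was used. In an equivalence trial, uneven loss of poor outcomes can make two arms look more alike than they are. The PP set offers no cross-check: it either omits such a patient or counts as a completer someone with no 52-week ODI.

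**Working it through.** **Step 1: the rules side by side, for an SAE patient without a 12-month ODI.**

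| Label or rule | Primary ODI value | PP status |
|---|---|---|
| Subject dropout | Failure by NRI | Out, as a non-completer |
| Discontinuation, read at patient level | Missing | In, counted as completed |
| General rule for missing efficacy data | Not imputed | Not addressed |

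NRI assigns a category to a responder endpoint. The primary endpoint is a continuous ODI change with no responder definition, so a failure has no number that can enter a mean difference. In practice all three rows leave the patient without an ODI value in the primary contrast unless the 52-week questionnaire is collected.

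**Step 2: the trial-level reading.** If discontinuation means stopping the whole trial, patients not yet at 12 months would have missing ODI and still count as PP completers. That pair of rules also needs repair.

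**Step 3: the follow-up duty.** The duty to follow up dropouts is broad, but the only evaluation it names is for safety. The Schedule of Activities has ODI at 2, 12, 24 and 52 weeks, and no sentence says these visits continue after dropout or that the values are used.

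**Step 4: possible size.** Let p1 and p2 be the proportions of each arm lost because of an SAE, and e1 and e2 the excess 12-month ODI in those patients. The mean difference over all patients contains p1·e1 − p2·e2. An analysis without these patients does not, so that amount is hidden. With a common excess e it is (p1 − p2)·e. The document gives neither SAE rates nor a deficit, so these are assumptions:

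| Loss through SAE | e = 10 | e = 40 |
|---|---|---|
| 5% vs 5% | 0 | 0 |
| 10% vs 5% | 0.05 × 10 = 0.5 (4% of 12.8) | 0.05 × 40 = 2.0 (16%) |
| 15% vs 5% | 0.10 × 10 = 1.0 (8%) | 0.10 × 40 = 4.0 (31%) |
| 20% vs 5% | 0.15 × 10 = 1.5 (12%) | 0.15 × 40 = 6.0 (47%) |

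**Step 5: what that means for the decision.** The plan's figure is 60 per group with 20% loss, so 60 × 0.80 = 48 are evaluable. The t-based two one-sided tests calculation (SD 18.8, margin 12.8, 5% per side, 90% power) gives 48, hence 48/0.80 = 60, so the figure reproduces on that basis. The stated decision rule uses a 95% CI, and the rest of this step uses that rule.

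- SE = 18.8 × √(2/48) = 3.84.
- P(equivalence | d) = Φ((12.8 − d)/SE − 1.96) − Φ((−12.8 − d)/SE + 1.96).
- Results: 83% at d = 0, 71% at d = 3, 42% at d = 6.

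If a true difference of 3 points came wholly from SAE patients and they were lost, the chance of declaring equivalence would be 83% instead of 71%. At 6 points it would be 83% instead of 42%. Both differences lie inside the margin, so these figures show how far the loss can move the result. They are not false-positive rates.

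**The case against.** A reader might infer that surgical failures are bound to leave the primary comparison. The document does not support that. Both lists are discretionary, so an SAE patient may simply stay in follow-up. The FAS decides, is analysed as randomized, and has no SAE exclusion. Treating dropouts as failures shows an intention to keep poor outcomes in. The follow-up duty covers dropout for any reason. All of this stands, and it limits the point to what the rules permit.

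A reader might also infer that the bias always favours equivalence. It does not. The hidden amount is zero when rates and deficits are equal. If the arm with more SAEs does better otherwise, losing those patients can widen the observed difference. Fewer patients also widen the CI, which works against equivalence.

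The first list speaks of discontinuing the study and the second of subject dropout, so they may describe different events. That reading is open. But the discontinuation list cites events in subjects, and the PP clause reads as patient-level. The ambiguity is part of the problem.

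Finally, the magnitude rests on assumed inputs and on every such patient being lost. AEs are recorded regardless of causality, so a uniform ODI deficit after any SAE is doubtful. That is why a range is shown.

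**Conclusion.** The point holds as a contradiction in stated rules with a conditional consequence. An SAE appears in both lists, the data rules attached to the two labels conflict, NRI is undefined for this endpoint, and continued collection and use of the 52-week ODI is not stated. Patients with poor surgical outcomes can therefore leave the primary comparison, and this can bias the equivalence result if SAE rates or deficits differ between arms. Under the assumed ranges the hidden difference is 0.5 to 6.0 points; it assumes that all such patients are lost and that the deficit is the same in both arms. This is not detail left to a statistical analysis plan: the protocol itself states the conflicting rules, and an ODI that was not collected cannot be recovered at analysis.

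**What to change.** Reconcile the Discontinuation and Drop-out Criteria with the analysis rules:

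- Define termination of the trial and withdrawal of a subject as separate events.
- State that SAEs, non-compliance and protocol deviations do not end outcome collection. ODI and the other questionnaires continue to 52 weeks unless the patient withdraws consent to data collection. Telephone collection can be used where needed; the Study design section already allows it when a visit is unavoidably missed.
- State that collected values are used as observed in the FAS.
- Limit the missing-data clause and the counted-as-completed clause to termination of the trial, and do not count a patient without a 52-week ODI as a PP completer.
- Replace the NRI and no-imputation rules for the primary endpoint with one missing-data rule suited to a continuous outcome.

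The cost is wording in these sections and a few extra follow-up contacts by existing staff.
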